# Implementation of an intervention to scale up coverage of pneumonia management in children younger than 5 years in a north Indian district: protocol for a quasi-experimental, mixed-methods, pre-post implementation study

**DOI:** 10.1136/bmjopen-2024-093705

**Published:** 2025-07-07

**Keywords:** Implementation Science, INFECTIOUS DISEASES, Community child health, QUALITATIVE RESEARCH, Child, Public health

## Abstract

**Abstract:**

**Introduction:**

The National Family Health Survey-5 has reported an under-five mortality rate of 41.9 per 1000 live births in India. Pneumonia, one of the leading causes of under-five mortality, contributes substantially to this figure. The Indian government has made efforts through multiple national programmes, but pneumonia-specific mortality remains high. The Government of India revised their Childhood Pneumonia Management Guidelines in 2019 to improve under-five pneumonia prevention and management. This implementation study aims to achieve a high population-based coverage of pneumonia treatment for under 5 yearold children in the Palwal district of India.

**Method and analysis:**

This implementation study uses a quasi-experimental pre-post design and a mixed-methods approach, conducted in three phases: (i) formative research, (ii) model optimisation through iterative testing in a learning block and (iii) scale-up and concurrent evaluation. The study is set in Palwal district, Haryana, and the primary catchment/study area will be the Health and Wellness Centres, the most accessible public health facilities for the community. Approximately 4167 households will be surveyed to capture ~2400 under-five children, among whom about 120 pneumonia cases (based on an estimated 5% prevalence) will be included in the analysis of treatment coverage and outcomes. Quantitative data will be analysed using descriptive statistics and generalised linear models, while qualitative data from focus group discussions and in-depth interviews will be thematically analysed using NVivo software.

**Ethics and dissemination:**

Ethical approval was granted by the ethical committees of the Society for Applied Studies (ERC/IR Pneumonia/2021), the Regional Ethics Committee of Western Norway (2022/531608) and the WHO(ERC.0003652). Additionally, this study has obtained the Government of Haryana state (Memo no. HSHRC/2022/505) and Health Ministry steering committee (approval date: 19 Dec 2022, proposal id 2022–17596) approvals. Informed consent will be obtained from all participants, including caregivers and healthcare workers, prior to data collection. Dissemination meetings in the study country will share results with stakeholders, including Ministry of Health officials, health managers, families of under-five children, community leaders and academia, to discuss national health programme implications. Results will also be shared regionally and globally, with publications and presentations encouraged in national and international forums.

**Study registration:**

Clinical Trials Registry – India, CTRI/2021/03/031622.

STRENGTHS AND LIMITATIONS OF THIS STUDYUses a quasi-experimental pre-post design with mixed-methods to capture both outcome and process-level insights.Follows an iterative, adaptive implementation cycle that incorporates continuous learning and real-time strategy refinement.Employs systematic household sampling and Probability Proportional to Size methods to ensure representative quantitative data collection.Uses a broad operational definition of pneumonia based on caregiver-reported signs, which may reduce specificity and lead to misclassification.Relies on self-reported data for key indicators, introducing potential recall and reporting biases.

## Introduction

 The National Family Health Survey-5 (NFHS-5), conducted from 2019 to 2021, reported an under-five mortality rate of 41.9 per 1000 live births in India.^1^ Data from national surveys between 2016 and 2018 revealed that the top three causes of under-five deaths in India were lower respiratory infections (17.9%), neonatal preterm birth (15.6%) and other neonatal disorders (14.3%).^2^ Among infectious diseases, pneumonia is the primary contributor to under-five mortality, accounting for 15%.^3^ There are estimated 30 million annual cases of acute respiratory illness (ARI), including 3 million cases of severe pneumonia. These statistics highlight the critical public health concern posed by under-five pneumonia and its substantial impact on India’s goal to reduce under-five mortality to 23 per 1000 live births by 2025.^4^

Over the years, the Indian government has consistently supported pneumonia control measures through multiple national programmes, such as Home-based Newborn Care (HBNC), Home-based Young Child Care, Integrated Management of Neonatal and Childhood Illness, Facility-based Integrated Management of Neonatal and Childhood Illness, Poshan Abhiyan, Mother’s Absolute Affection programme, Universal Immunisation Programme/Mission. Indra Dhanush, Vitamin A supplementation, Infant and Young Child feeding programme and Facility-based Newborn Care, to address childhood infections prevention and enhance under-five infection management.^4^ Despite these efforts, India still witnesses an annual pneumonia-specific mortality of 0.14 million.^4^ Only 22% of caretakers seek appropriate care for acute respiratory infections due to factors like limited awareness, financial constraints, healthcare accessibility issues, reliance on home remedies and insufficient community involvement.^5^ Front-line health workers also face challenges, lacking the necessary skills and resources.^6^ Evidence from previous studies in India indicates that gender disparities exist in healthcare-seeking behaviour, with girls often receiving delayed or inadequate treatment for childhood illnesses, including pneumonia, necessitating a focused effort to promote equitable care through targeted strategies for female children.^7^ The primary challenge lies in the effective implementation of these well-intentioned national guidelines and programmes.^4^

Considering the substantial burden and the pressing need to intensify under-five pneumonia prevention and management efforts, the Government of India (GoI) launched the Childhood Pneumonia Management Guidelines in 2019.^4^ These guidelines represent a comprehensive shift from previous fragmented efforts by emphasising structured case management pathways across all levels of the health system. Key features of the CPMG include standardised management using oral amoxicillin and injectable gentamycin for pneumonia and possible serious bacterial infections (PSBI); use of pulse oximeters to assess severity, pre-referral treatment and referral mechanisms, integration of pneumonia indicators into the Health Management Information System (HMIS) and guidance for health system strengthening, including staff capacity building, community engagement and logistics support. In pursuit of ensuring the programme’s visibility and long-term sustainability, the Social Awareness and Actions to Neutralise Pneumonia Successfully (SAANS) campaign was initiated, aligning with the Protect, Prevent and Treat interventions for childhood pneumonia.^4 8^ This annual campaign runs from November 12th (World Pneumonia Day) to February 28th and aims to raise awareness among caregivers and communities about pneumonia prevention, recognition and treatment, which may eventually reduce the pneumonia burden.^4^ It mobilises Accredited Social Health Activists (ASHAs) and other front-line workers to conduct community outreach, home visits and behaviour change communication while promoting increased demand for pneumonia services. The strategic vision revolves around the utilisation of Health and Wellness Centres (HWCs), established under the Ayushman Bharat Yojana, as central nodes for early identification, treatment and timely referral of severe cases of under-five childhood pneumonia to tertiary healthcare facilities for life-saving interventions.^4^ Despite these advances, the full-scale implementation of the CPMG and SAANS initiatives has been limited in several states due to health system disruptions, particularly during the COVID-19 pandemic. Additionally, effective implementation of the CPMG hinges on several elements: accurate community-level case identification, trained providers, well-equipped health facilities and functional referral systems. Previous studies in India have shown that frontline workers often lack the required knowledge and confidence to follow pneumonia management protocols, and facilities frequently struggle with infrastructure and medicine shortages.^9^,^11^

Considering the above context, this implementation research was conceptualised to optimise and evaluate the delivery of the GoI’s Childhood Pneumonia Management Guidelines^4^ in a resource-constrained setting. The study focuses on achieving high population-based treatment coverage, defined as 80% or more under-five children receiving the full recommended treatment while aligning with and strengthening existing public health infrastructure. This study specifically aims to address several of these persistent barriers such as delayed care-seeking, low treatment compliance, inadequate provider capacity and limited adherence to national pneumonia management protocols, through a locally adapted implementation strategy. The research will identify practical implementation barriers and develop adaptable strategies that can inform scale-up efforts in similar settings across India.

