#### Primary objective

To develop, refine, implement and evaluate an optimised, sustainable and scalable implementation model for improving population-based coverage of pneumonia management among under-five children, in alignment with the GoI’s Childhood Pneumonia Management Guidelines.^4^ The model aims to achieve ≥80% treatment coverage in the target population.

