### Sample size

A recent study in the same district found that the prevalence of pneumonia among under-five children in the last 2 weeks was around 5%.^15^ Currently, approximately 25% of under-five children seek appropriate care for ARI, indicating a programme coverage of around 25%.^5 16^ With the introduction of the new implementation strategy, we expect an increase in pneumonia treatment coverage by 80%. To account for potential non-response and to estimate 80% coverage of appropriate treatment at baseline and end-line surveys for under-five children with pneumonia cases (as per the operational definition), a conservative sample size of 120 is to be included. Additionally, based on these assumptions, the estimated sample size at a 5% level of significance for each survey (baseline and end-line), and a varied range of coverage is shown in figure 2.

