### Outcomes

The primary outcome of the study is to find the coverage of effective pneumonia management (ie, management done as per the childhood pneumonia management guidelines of India) from appropriate sources. Appropriate sources refer to government and/or private healthcare facilities like HWCs, PHCs, CHCs, DHs, private clinics/hospitals, etc, where treatment is provided by qualified healthcare practitioners. In contrast, non-appropriate sources include unlicensed practitioners, chemists, traditional or religious healers, and others who are non-registered medical healthcare workers. The secondary outcomes are total recovered cases after 7 days of treatment, treatment failure, compliance to management as recommended by healthcare providers, in-patient case duration and treatment provided, and gender-wise distribution of diagnosed, treated and complaint cases.

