### Description and tracking process of study outcomes

The primary targeted outcome of this study is achieving ≥80% coverage of appropriate pneumonia management and will be assessed using a structured quantitative household survey tool. Three cross-sectional surveys (baseline, midline and endline) will be conducted with caregivers of under-five children who experienced pneumonia-like symptoms in the previous 28 days. These surveys will capture whether care was sought from appropriate sources and whether treatment received aligned with the national guidelines. The success of this research will be when at least 80% of these children:

Received care from appropriate sourcesWere managed according to the recommended national protocols with ≥80% compliance to the prescribed treatment.

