### Intervention package

The intervention package will be aligned with the GoI guidelines, which include early identification of pneumonia cases through ASHAs and empowering families, prompt care-seeking from appropriate providers for pneumonia treatment and prompt referral of severe pneumonia cases with pre-referral treatment. At the outpatient department (OPD) of facilities (HWCs/PHCs/CHCs/DH), treatment providers need to be available, be competent and have access to appropriate logistics (equipment, regular supplies of medicines). Pulse oximeters will be provided at the OPDs of these facilities to assess oxygen saturation for improved assessment/evaluation of severe cases requiring referral.

For children, (0–59 days) with PSBI, a prereferral dose of gentamicin and amoxicillin will be provided by the health workers at the HWCs, and then cases are referred to higher facilities. But if a referral is not possible/denied, the package also aims to provide treatment to children aged 0 to 59 days in the outpatient department of primary-level care. In cases where caregivers are unable to bring their infants to the health facilities for the full course of injection, gentamycin and oral amoxicillin for 7 days will be provided by the auxiliary nurse midwives to cases (0–59 days) at home.^4 19 20^

In discussions with the government, strategies will be finalised to promote treatment in female children, such as providing additional incentives to ASHAs for referring or accompanying girl children for pneumonia treatment, free transportation for girl children to facilitate referral for outpatient treatment and providing free food or compensating daily wages lost due to hospital admissions.

At the post-facility level, ASHAs will be rewarded (with government consensus) for ensuring full compliance with the treatment course in female children. The decision to address the appropriate treatment of pneumonia in the private sector, where many children with pneumonia seek care, by involving private providers in the discussion with the government partners, will be based on the formative research findings. Appropriate use of bronchodilators in children with wheeze at health facilities and identification of conditions mimicking pneumonia for rational therapy will also be included. Finally, recognition of cases that do not have pneumonia and do not require antibiotics but may benefit from supportive treatment.

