The research findings from the learning block will be used to enhance Model 0+, leading to the development of Model 1. Subsequently, a series of rapid cycles involving concurrent implementation, monitoring and strategy refinement will be conducted in the remaining six HWCs. These iterations will take place in multiple co-design workshops, with significant involvement from government authorities. The iterative process will continue until an optimised and comprehensive strategy/model is achieved with the potential for achieving high coverage and quality of pneumonia management among under-five children in the study areas (figure 4). The model will be considered optimised when the healthcare providers can consistently recognise pneumonia signs and symptoms and manage cases in accordance with the national guidelines, with ≥80% fidelity among the suspected cases visiting the centres. Second, treatment compliance among under-five children reaches at least 80%, who have received this treatment from the health facilities.

Once the model is optimised, it will be scaled up to all ten HWCs in the study area. During this scale-up phase (estimated to last 7–8 months), we will continue to monitor both implementation barriers and quantitative indicators such as fidelity to the guidelines and treatment compliance. At the conclusion of the scale-up phase, an endline household survey will be conducted using PPS sampling to identify 120 under-five children who had pneumonia symptoms in the past 28 days. These data will be compared with baseline measurements to assess changes in key outcome indicators, i.e. under-five pneumonia cases receiving management (as per the national guidelines) from the appropriate health facilities, which determines the coverage of appropriate pneumonia management.

The final findings will be shared with state- and district-level health authorities in Haryana. If the district government expresses interest and supports the approach, the model, having already been scaled up within the study area, may be adopted for implementation across the entire Palwal district, with continued technical support from the research team.

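### The 80% success criterion counts treatment compliance; the primary outcome and the baseline-endline comparison do not, so the same survey can pass or fail

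*Protocol article*

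**What the plan says.** The 80% target appears in several places in the protocol article, with different content.

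- **Introduction:** high coverage is "defined as 80% or more under-five children receiving the full recommended treatment". No source of care is mentioned.
- **Primary objective:** "The model aims to achieve ≥80% treatment coverage in the target population". Coverage is not defined there.
- **Outcomes:** the primary outcome is "coverage of effective pneumonia management (ie, management done as per the childhood pneumonia management guidelines of India) from appropriate sources". Compliance is listed separately, as the secondary outcome "compliance to management as recommended by healthcare providers".
- **Description and tracking process of study outcomes:** success means that at least 80% of the surveyed cases received care from an appropriate source and were "managed according to the recommended national protocols with ≥80% compliance to the prescribed treatment".
- **Implementation strategy:** the baseline-endline comparison concerns "under-five pneumonia cases receiving management (as per the national guidelines) from the appropriate health facilities, which determines the coverage of appropriate pneumonia management". Compliance is absent.

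The same Implementation strategy section gives the rule for calling the model optimised: at least 80% fidelity among suspected cases visiting the centres, and compliance of at least 80% among children treated at the facilities. There the compliance figure is a group rate.

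For planning, the Sample size section says that "approximately 25% of under-five children seek appropriate care for ARI, indicating a programme coverage of around 25" per cent.

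**The concern.** The study makes one success claim, and its numerator changes between sections. Compliance is inside the success criterion, outside the primary outcome, and outside the comparison that is said to determine coverage. The Introduction's full treatment is stricter again than 80% compliance. Within the success criterion, the compliance figure could be a threshold that each child must reach or a rate for the group.

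This is a contradiction in the stated decision rule, not a detail left to a later analysis plan. If it stays open, the definition could be chosen once the endline data are in hand, and a coverage figure near 80% could be reported as success or failure on the same records.

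**Working it through.** **1. The plan's own figures.** The inputs are 120 cases, 5% prevalence, 12% of the population under five and a household size of 4.8 (Sample size).

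- Children: 120 / 0.05 = 2400.
- Households: 2400 / (0.12 × 4.8) = 2400 / 0.576 = 4166.7, rounded up to 4167.

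Both reproduce. With 120 cases, the 95% half-width at 80% is 1.96 × √(0.8 × 0.2 / 120) = 0.072, or 7.2 points, treating the cases as a simple random sample.

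**2. The definitions side by side.**

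| Section | Appropriate source | Guideline management | Compliance |
|---|---|---|---|
| Introduction | not stated | full recommended treatment | implied complete |
| Outcomes | required | required | secondary outcome |
| Success criterion | required | required | at least 80%, level not stated |
| Implementation strategy (baseline v endline) | required | required | not mentioned |

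**3. The article's own minimum values.** The optimisation rule gives fidelity 0.80 and compliance 0.80. Three assumptions are needed: all cases reach an appropriate source (1.00), the facility rates carry over to the surveyed cases, and compliance is the share of guideline-managed children who meet the threshold.

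- Without compliance: 1.00 × 0.80 = 0.80, or 96 of 120. Success.
- With compliance in the same child: 1.00 × 0.80 × 0.80 = 0.64, or about 77 of 120. Failure.
- With compliance as a separate group rate: coverage 80% and compliance 80%. Both pass.

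The 16-point gap is more than twice the half-width of 7.2 points.

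**4. How wide the zone of disagreement is.** Let g be coverage without compliance and c the compliance rate among those children. The two definitions disagree when g is at least 0.80 and g × c is below 0.80, that is, for g from 0.80 up to 0.80 / c.

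- c = 0.80: g from 80% to just under 100%.
- c = 0.90: 0.80 / 0.90, so g from 80% to 88.9%.
- c = 0.95: 0.80 / 0.95, so g from 80% to 84.2%.

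With equal rates at all three steps (assumed, since the documents give none):

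| Rate per step | Source and guideline | With compliance |
|---|---|---|
| 95% | 90.3% | 85.7% |
| 90% | 81.0% | 72.9% |
| 85% | 72.3% | 61.4% |

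The verdict differs only in the middle row. Reaching 80% needs an average step rate of √0.8 = 89.4% with two steps and 0.8^(1/3) = 92.8% with three.

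**5. The 25% planning figure.** Children managed by the guideline at an appropriate source are a subset of those who sought appropriate care. If the care-seeking figure for acute respiratory illness applies to the surveyed cases, baseline coverage under the Outcomes definition is at most 25%. This does not undermine the sample size: detecting 25% against 80% needs only about 12 cases per survey (two-sided 5%; 80% power assumed), so the 120 is not driven by that contrast.

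**The case against.** The sections can be read as compatible. Outcomes names the primary outcome, and the tracking section says how it is measured. Its two conditions follow one phrase about the same children, so the ordinary reading is that both must hold in the same child. A component of a composite may also be reported as a secondary outcome, and the Introduction's sentence is shorthand for what counts as high coverage. Much of this stands. What it does not explain is why the baseline-endline comparison, written later in the article and said to determine coverage, omits compliance, or whether the compliance figure is per child.

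It also stands that the verdict changes only in a band of results, as step 4 shows.

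Two stronger readings are tempting, but the documents do not support them.

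- A reader might count care-seeking as a further rival definition of the outcome. The Sample size section uses it only as a planning proxy; no section makes it the outcome or the success criterion.
- A reader might infer that the Introduction's wording caps coverage and rewards over-treatment, because the case definition is admitted to have low specificity and children without pneumonia could never count as treated. That equates full recommended treatment with antibiotics, which the Introduction does not say. The intervention package includes "recognition of cases that do not have pneumonia and do not require antibiotics but may benefit from supportive treatment", so supportive care may be the recommended management. The documents also give no share of true pneumonia from which to compute a cap. What remains is narrower: the article does not say how such children are counted.

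**Conclusion.** The point holds as an inconsistency in the decision rule. The success criterion includes compliance; the primary outcome and the baseline-endline comparison do not; the Introduction's wording is stricter than either; and the level of the 80% compliance figure is not stated. At the article's own minimum values the difference is 80% against 64%, given full appropriate care-seeking, facility rates that carry over to the surveyed cases, and compliance counted as a share of children. If compliance is higher, the band of disagreement narrows, and with every step at 95% both definitions pass. No size can be put on the difference between full treatment and 80% compliance, because the article gives no data on how complete treatment is. The 25% baseline is a proxy mismatch of lesser weight.

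**What to change.** Before coverage is analysed, state one child-level definition and use it in the Introduction, Primary objective, Outcomes, the success criterion and the endline comparison under Implementation strategy. There are two consistent options:

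- make the success criterion the primary outcome, with appropriate source, guideline management and compliance all required in the same child; or
- remove compliance from the success criterion and keep it as a secondary outcome.

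The study team must reconcile which applies. Whichever is kept:

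- State whether the 80% compliance figure is a per-child threshold or a group rate.
- Report source, guideline management and compliance as a cascade, so that readers can see coverage under either definition.
- In Sample size, relabel the 25% as care-seeking and describe it as an upper bound for baseline coverage under the Outcomes definition.
- Say how survey-defined cases found not to have pneumonia are counted. Provider classification is not among the listed household items, so this must rest on caregiver report or be stated as a limitation.

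The cost is mostly wording. The household survey items under Data collection for monitoring progress already cover source, type of treatment and compliance. Classification at the visit cannot simply be added: baseline data were collected in June to August 2023 and the endline survey was scheduled for February to April 2025. The downside is that the stated coverage may be less favourable than if each component were judged separately.
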